#### General procedures for follow-up data collection

Follow-up data will be collected via telephone survey. These call attempts will be made on multiple days at different times of the day. After approximately five call attempts with no answer, or two voicemail messages, the study staff will mail a letter stating that we are attempting contact. About a week after the letter is mailed, we will attempt one more ‘round’ of calls. Calling will continue until attempts to reach the participant have been exhausted (determination that there are no working telephone numbers), participants have completed the survey or declined participation, or the participant is more than three weeks past their survey due-date.

#### Chart review

Chart review procedures will be worked out with each CHC, who can opt in or out of this review. We aim to recruit at least 10 of our 16 CHCs to participate in the chart review, recognizing that such a procedure is onerous for CHCs without a flexible electronic medical record system. Chart review data will be used to supplement and support the self-report findings. We aim to review 74 charts per CHC.

#### Provider-level data

To understand how the implementation strategies (and the study) are perceived by the people who work at the health center and to assess whether strategies directed at providers actually reached them, we will also conduct brief, anonymous surveys of health center employees. Surveys will be distributed at the start of the study and post-intervention. In general, these questions will address RE-AIM principles, including implementation, perceived maintenance, feasibility, acceptability, but we may add questions to the post-intervention survey based on experiences and feedback during implementation. To maximize response, this survey will be brief (one page) and can be mailed in a pre-paid envelope, or faxed to a secure fax machine. For example, if a CHC chose to develop provider reminders in their electronic record, the post-survey would ask if the provider had seen the reminder and what they thought about it.

#### Practice-level data

We will conduct an organizational assessment by interviewing clinic administrators in order to address reach, implementation, and maintenance of the intervention and implementation strategies. Interviews will be audiotaped and transcribed, when the interviewee consents. This semi-structured interview will cover: patient characteristics, current efforts to promote CRC screening if any, current CRC screening rates, current efforts to promote other preventive care or disease management, perceived need for change, preferred changes, and barriers to implementation. The research team will work with the CHC data manager, if necessary, to access some of this information. We will ask our initial contact at the health center to recommend other persons with whom we should speak, such as other level managers, chief operating officers, medical directors, quality improvement personnel, or opinion leaders within the practice. Data, when presented, will be de-identified (both to individual and to health center). Any characteristics that could be used to identify the administrator or the health center/health system will be masked or aggregated. Data will be used to inform the intervention development, but may be analyzed later (*e.g.*, to look at characteristics of CHCs that did or did not change screening rates). We will aim to conduct at least two interviews per participating site.

#### Retention of health centers and survey respondents

We will use multiple evidence-based methods to maximize retention. We do not anticipate site-level attrition once a CHC is enrolled, because CHCs are entitled to pick and choose which strategies they wish to implement and the data collection burden on them (organizational assessment and exit interview) is designed to be minimal. However, the participatory process can be burdensome and time-consuming, or perceived burden could deter sites from participation. Our procedures are designed to balance fidelity to CBPR with reducing ‘what we ask’ from participating sites. CHCs are reimbursed financially for all phases of the study, though this does not truly capture the time they spend in a participatory approach.

Attrition among patient participants is a potential limitation. We will apply best practices for retention
[50-53] and collect complete contact information at enrollment (name, postal address. and at least two telephone numbers). Participants will be asked to list a secondary contact person as a locator. Differential attrition in the patient survey by study arm is unlikely because the intervention is at the center-level and sites are randomized.

We expect some attrition amongst health center employees, more so due to turnover within CHCs than because of the study. Our post-survey will ask how long the respondent has been at the health center, but because these surveys are not identifiable and not linked, we will not know whether the same people answered a staff survey at pre and post evaluation.

#### Outcomes and analysis

Our analysis will examine rates of being up-to-date on CRC screening, accounting for the clustered nature of the data. We will also assess which CHCs were reached by the study (and how representative they are of area CHCs), reach of the intervention within a CHC (who was ‘touched’ by the intervention, which strategies were adopted, implementation of strategies, and maintenance of the strategies by analysis of our organizational assessments, staff surveys, and qualitative feedback.

#### Power

This study was powered based on patient self-report of screening. With16 CHCs (n = 74 participants per cluster) and intra-class correlation at 0.04, we will have 80% power to detect a 15% point difference in screening between intervention and comparison. Prevalence rates are estimated based on our experiences with similar patient populations, local BRFSS data, and published screening rates. Intervention effects were estimated from the rough average of published percent increases in screening for our potential strategies. These strategies resulted in a range of 12 to 18 percentage point differences
[54-64]. If intra-class correlation is higher but the impact is greater, we still maintain at least 80% power with this sample.

#### Analysis

Descriptive analysis will be used to characterize reach, external validity, adoption of strategies, and fidelity to implementation. Effectiveness of the intervention in increasing CRC screening will focus on self-reported patient completion of CRC screening at 12 months post-baseline. Statistical analysis will quantify the intervention effect at the cluster (CHC) and individual (patient) levels. For the individual-level analysis, we will use a generalized linear mixed model, adjusting for individual-level covariates, and cluster-level covariates, and accounting for the clustered nature of the data. Confounders will be identified as those variables that might influence the outcome and their association will be tested in a bivariate model. Variables that are significantly associated with the outcome will be included as potential covariates in the final adjusted model.

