#### Patient-level data

The baseline survey will include: demographics, healthcare utilization, medical home, cancer screening, literacy
[46], behavior intentions, barriers to CRC screening
[47-49], and knowledge about colon cancer. Standard measures from national surveys are used as available. The six-month and 12-month surveys include self-reported CRC screening, healthcare utilization, and awareness of screening or educational efforts. CHCs may add site-specific questions if they wish.

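### Covariates for the patient-level effectiveness model are chosen by significance against the trial's own outcome and are not limited to baseline variables, so the model depends on the outcome data and may absorb part of the intervention effect

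*Protocol article*

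**What the plan says.** The effectiveness question is set in the Analysis section: "Effectiveness of the intervention in increasing CRC screening will focus on self-reported patient completion of CRC screening at 12 months post-baseline". The effect is to be quantified at both CHC and patient level. For the patient level, "we will use a generalized linear mixed model, adjusting for individual-level covariates, and cluster-level covariates, and accounting for the clustered nature of the data".

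Two sentences then fix how covariates are found. First: "Confounders will be identified as those variables that might influence the outcome and their association will be tested in a bivariate model". Second: "Variables that are significantly associated with the outcome will be included as potential covariates in the final adjusted model". The section gives no candidate list, significance threshold or time point for the candidates.

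The Patient-level data section shows what is available. At baseline: "The baseline survey will include: demographics, healthcare utilization, medical home, cancer screening, literacy", followed by intentions, barriers and knowledge. At follow-up: "The six-month and 12-month surveys include self-reported CRC screening, healthcare utilization, and awareness of screening or educational efforts". Healthcare utilization therefore exists in both a baseline and a follow-up version, and the rule does not say which one is a candidate.

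**The concern.** In a randomized trial, association with the outcome does not make a variable a confounder. Adjustment is useful for precision and for chance imbalance, and for both purposes the covariates should be prognostic, measured before the intervention can act, and named in advance. The stated rule asks only whether a variable is associated with the outcome.

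Two things are at stake. First, the adjusted model is settled only after the outcome has been seen, and the word potential in the second sentence leaves a further choice open. Second, the variables most likely to pass such a test include some that the intervention is meant to move. Patient reminders, provider reminders and provider feedback are intended to bring patients to screening, partly by making them aware of it and prompting contact with care. Follow-up awareness and utilization can thus meet the written criterion, and conditioning on them removes part of the effect the trial is designed to estimate.

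**Working it through.** **1. The plan's own figure, for scale.** The Power section says "we will have 80% power to detect a 15% point difference in screening between intervention and comparison", with 16 CHCs, 74 patients each and an intra-class correlation of 0.04. Eight CHCs per arm and two-sided alpha 0.05 are assumed.
- Design effect: 1 + (74 − 1) × 0.04 = 3.92.
- Effective sample size per arm: 8 × 74 / 3.92 = 151.0.
- No comparison rate is given numerically. Power for 15 points is 83.5% at a rate of 20%, 79.8% at 25%, 74.5% at 40% and 79.8% at 60%. With a t reference on 14 degrees of freedom it is 69.0% at 40%.

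The stated 80% is thus reached near 25% or 60%. The covariate point does not depend on it; 15 points serves only as the yardstick.

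**2. A follow-up variable on the causal pathway.** Assumptions: comparison rate 40%; the variable rises from 30% to 60% under intervention; it carries half of the 15 points.
- Its coefficient is 0.075 / 0.30 = 0.25.
- Total effect: 0.075 direct + 0.25 × 0.30 through the variable = 0.15.
- Adjusted for the variable, only the direct 0.075 remains.

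Simulation (16 × 74, linear random-intercept model standing in for the generalized linear mixed model, ten patient-level baseline candidates of which five are prognostic, screen at p < 0.05, t reference, 1,500 runs): the mean estimate fell from 0.148 to 0.072 and power from 69% to 23%. The unadjusted 69% agrees with the t-based figure in step 1.

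**3. A follow-up variable that shares an unmeasured cause with screening.** No true effect on screening, but the intervention changes the variable. After screening it in, the mean estimate was −0.043, and type I error was 12.1% against 5.1% unadjusted (1,500 runs).

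**4. Selection among baseline variables only, no true effect, t reference.**

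| Candidates | Unadjusted | After screening |
|---|---|---|
| 10 patient-level (3,000 runs) | 4.7% | 4.6% |
| 10 patient-level (second run, 1,500) | 4.8% | 5.2% |
| 10 patient-level + 5 CHC-level noise (3,000 runs) | 4.7% | 5.3% |
| 10 patient-level + 8 CHC-level noise (1,500 runs) | 5.0% | 4.7% |

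If the analyst could also pick the smallest p-value among the unadjusted, full and leave-one-out models, the 1,500-run settings gave 5.9% (patient-level only) and 10.5% (with eight CHC-level candidates).

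**5. Few clusters versus selection.** Logistic mixed model, random-intercept SD 0.418 on the logit scale, 45% rate, no effect, six CHC-level noise candidates, 4,000 runs.

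| Model | Wald z | t reference |
|---|---|---|
| No covariates, no selection | 8.5% | 5.9% |
| One prespecified CHC-level covariate | 9.1% | – |
| Screen at CHC level | 8.4% | 6.2% |
| Screen ignoring clustering | 10.6% | 7.8% |

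A cluster-level approximation with the same rate and SD gave 9.5%, 9.9% and 12.0% for Wald z (no covariates, CHC-level screen, clustering-blind screen), and 5.4% to 5.8% throughout with a t reference.

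**6. CHC-level noise variables in a clustering-blind screen.** The test statistic is inflated by √3.92 = 1.98. The chance of passing is P(|Z| > 1.96 / 1.98) = P(|Z| > 0.99) = 32%, which simulation reproduces.

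**The case against.** The best defence is that the article does not say follow-up variables will be adjusted for. It calls the candidates confounders, a term that ordinarily excludes variables on the causal pathway. It uses the patient surveys to judge whether materials reached patients, which places awareness under implementation. It lists many baseline variables that are natural candidates. Screened variables become only potential covariates, and a CHC-level analysis is planned as well. All sites also get access to patient education materials, so awareness of those may differ less between arms. All of this stands, and it makes the mediator problem something the rule permits rather than a stated plan. It does not remove the defect: the rule defines confounders by association with the outcome alone, and nothing in it excludes the follow-up surveys.

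It could also be said that a covariate list belongs in the full protocol or analysis plan. That would answer a complaint of missing detail. Here the article states a selection rule, and it is the rule that is at fault.

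Two stronger readings are tempting and not supported. A reader might infer that significance screening invalidates the final p-value, pointing to rejection rates of 9 to 10% under a true null. Step 5 shows that a Wald z test with 16 clusters already rejects 8.5% to 9.5% of the time with no covariates and no selection. Nearly all of the excess comes from the small number of clusters, and the article does not state the reference distribution. A reader might also infer that about a third of pure-noise CHC variables will be selected. That holds only if the screen ignores clustering, which the article does not state; it says the analysis accounts for clustering.

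**Conclusion.** The point holds in a limited form. The covariate rule makes the adjusted patient-level model depend on the outcome data, and it leaves open adjustment for follow-up utilization and awareness, which the intervention can change.

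The size depends on what enters:
- **Baseline variables only.** Type I error stays about where it is without selection. With a t reference, selection adds between nothing and about 2 points (7.8% − 5.9% = 1.9), and the upper end requires a clustering-blind screen of CHC-level variables.
- **A follow-up variable on the pathway.** A 15-point effect would be reported as about 7 to 8 points if half of it ran through that variable. The one-half is an assumption; no figure in the article supports or excludes it.
- **A follow-up variable sharing an unmeasured cause with screening.** Type I error was about 12% in an illustrative setting.
- **Open choice among potential covariates.** Up to 10.5% if the most favourable model were picked, which the article does not propose.

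The covariate counts, covariate strengths and comparison rates are assumptions, so these figures show scale and are not predictions.

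**What to change.** Delete the two sentences on bivariate screening and state instead:
- The individual-level model adjusts for a short set of covariates fixed before any 12-month outcome is examined, all measured at baseline.
- Up-to-date screening status at baseline is in the set. It is already collected and is an obvious prognostic variable for later status.
- Other patient-level baseline covariates are the sponsor's choice. CHC-level covariates are kept to very few, because each one uses between-CHC degrees of freedom and there are only 16 CHCs.
- No variable collected at six or twelve months enters the effectiveness model. Follow-up awareness and utilization are kept for the reach or mediation analyses.

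The cost is a few sentences, with no extra patients or data. The Trial status section says patient data collection has only begun, so the set can still be fixed before 12-month outcomes are examined. The downside is that a prognostic covariate nobody foresaw is left to a sensitivity analysis.

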#### Trial status

The trial is currently ongoing. The first set of health centers have been recruited and patient data collection has begun.

## Discussion

Increasingly, researchers are trying to balance randomized controlled research with community-based research aimed at decreasing disparities. Our research design is aimed at testing the effect of an implementation intervention to increase colorectal cancer screening, and at the same time assess the viability (and challenge) of translating evidence-based strategies into diverse settings. The implementation of interventions at the practice-level should mean that patients at the CHC have equal chance to be exposed to an intervention if and when they come for an appointment; other approaches that require patient uptake might disproportionately reach select groups of patients.

Our approach to health center recruitment will allow us to examine whether settings are representative, including examining reach and adoption (two key elements of the RE-AIM theoretical framework) by tracking how many settings were approached, how many participated, and reasons for non-participation
[65-68]. The assessment of participation and reasons for non-participation is a critical advancement toward scientific rigor.

Our decision for allowing a ‘menu’ of implementation strategies balances the ability to test intervention effects with a respect for the different contexts and preferences of each health center. We recognize that this approach is both a strength and a challenge in the current study. The challenge in our ‘menu’ design is that it will be difficult to know which strategy had impact, because CHCs can choose as few or as many as they want. However, our main question is whether the intervention approach of offering a menu of strategies is effective. Identifying the specific effect size of each individual strategy is secondary to the question of whether the overall approach can increase screening. We will carefully track organizational characteristics as well as which strategies are adopted and implemented by which CHCs. We plan to explore the differential effectiveness of strategies if there is enough variation. For these reasons, the menu approach strengthens our study and better informs both the literature and prevention practice.

Efforts at reducing disparities and increasing use of appropriate and recommended cancer screening must address the varying contexts in which primary care occurs and the many barriers to screening at the patient, provider, and clinic levels. Practical trials that address external validity, and strive to understand how interventions may (or may not) work in real-world settings are critical to reducing and ultimately eliminating disparities in cancer screening and survival
[65-68].

## Abbreviations

CRC: Colorectal cancer; CHC: Community health center.
